## Methods/design

### Study design

The study is a multicentre prospective longitudinal cohort study with a nested single-blind randomised controlled trial (RCT). The RCT is conducted using a subset of participants from the cohort study (Fig. 1) [46]. The protocol is described according to the Standard Protocol Items: Recommendations for Interventional Trials (SPIRIT) checklist for clinical trials (see Additional file 1 for the SPIRIT checklist). Participants are followed during the first 6 months post-injury. During this period, there are three measurement points: 2 weeks (T0), 3 months (T1) and 6 months (T2) post-MTBI (Figs. 2 and 3). The intervention begins 2–4 weeks post-injury and ends 6 months post-injury. The measurements and measurement times are the same for the cohort study and RCT participants. Measurements are performed by the researcher, who is blinded to the RCT group assignment.

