Sensory processing	Adolescent Adult Sensory Profile–Dutch version	AASP-NL	12–18	X		X

*PedsQL* Paediatric Quality of Life Inventory, *T0* 2 weeks after mild traumatic brain injury (MTBI), *T1* 3 months after MTBI, *T2* 6 months after MTBI

**Table 3 Tab3:** Outcome domains, measurement instruments and measurement moments for the caregivers

Domain	Measurement instrument	Abbreviation	Age (years)	T0	T1	T2
Activities and participation^a^	Child and Adolescent Scale of Participation–Dutch language version	CASP-DLV	All	X	X	X
Quality of Life	PedsQL–Quality of Life Scale	PedsQL-QoL	All	X		X
Fatigue	PedsQL–Multidimensional Fatigue Scale	PedsQL-Fatigue	All	X		X
Health and behaviour	Health Behaviour Inventory	HBI	All	X		X
Post-traumatic stress	Schokverwerkingslijst (Impact of Event Scale–Dutch language version)	SVL (IES)	All	X		X
Family functioning	Family Assessment Device–General Functioning Scale	FAD-GF	All	X		X
Behaviour and emotion	Child Behaviour Checklist	CBCL	All	X		X
Sensory processing	Sensory Profile–Dutch short version	SP-NL	6–11	X		X

*PedsQL* Paediatric Quality of Life Inventory, *T0* 2 weeks after mild traumatic brain injury (MTBI), *T1* 3 months after MTBI, *T2* 6 months after MTBI

^a^Primary outcome measure

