#### Cohort study

To determine the results of the primary outcome measure (CASP-DLV parent-reports), descriptive statistics will be used. Continuous variables will be expressed as the means and standard deviations or as medians with interquartile ranges, depending on the distribution values. Repeated-measures analysis of variance will be used to determine the difference in activities and participation over time. If a significant difference between the measurement points (*p* < 0.05) is found, a post hoc analysis based on Levene’s test will be performed.

Linear regression analysis will be used to identify the outcome predictors of activities and participation at 6 months post-injury, as measured by the CASP-DLV parent reports. Within 2 weeks after the injury, both continuous and categorical variables (i.e., injury and non-injury-related factors) are measured, as well as pre-injury family functioning (FAD-GF) and behaviour (CBCL); degree of fatigue (PedsQL-Fatigue); quality of life (PedsQL-QoL); sensory processing (SP/AASP-NL); physical, cognitive, emotional and behavioural post-concussive symptoms (HBI); post-traumatic stress (Schokverwerkingslijst [Impact of Event Scale–Dutch language version]); and participation in after-school activities (CAPE). Each variable will first be examined using univariate linear regression analysis to predict activities and participation. Next, variables with values of *p* < 0.2 in the univariate linear regression analysis will be included in the multivariate linear regression analysis. In the multivariate linear analysis, the significance level will be set at *p* < 0.05. For more clinically relevant purposes, outcome predictors will also be determined using logistic regression analyses. If the intervention is found to be effective (see statistical analyses of RCT study below), the data of the intervention group will be excluded from all of the cohort study analyses.

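### The predictor models for the 6-month CASP-DLV omit the 2-week score on the same scale, so they cannot show which factors add to early participation

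*Protocol article*

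**What the plan says.** In the protocol article, Statistical analyses, Cohort study, the target is the parent-reported CASP-DLV at 6 months: "Linear regression analysis will be used to identify the outcome predictors of activities and participation at 6 months post-injury". The candidates are then named: the injury and non-injury factors, FAD-GF, CBCL, PedsQL-Fatigue, PedsQL-QoL, the sensory profiles, HBI, the post-traumatic stress scale, "and participation in after-school activities (CAPE"). The selection rule follows: "Each variable will first be examined using univariate linear regression analysis to predict activities and participation". Variables with p < 0.2 go on to the multivariable model, tested at p < 0.05. The same section adds that "outcome predictors will also be determined using logistic regression analyses", with no separate predictor list.

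The CASP-DLV at T0, whether parent or self-report, appears neither in that list nor in Table 1. Yet Table 3 (Outcome measurements) has the "Child and Adolescent Scale of Participation–Dutch language version" completed by caregivers of children of all ages at T0, T1 and T2, and marks it as the primary outcome measure. Under Study design, "there are three measurement points: 2 weeks (T0), 3 months (T1) and 6 months (T2) post-MTBI", and "The measurements and measurement times are the same for the cohort study and RCT participants". The T0 score is therefore planned for the whole cohort. No reason is given for leaving it out.

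**The concern.** The early value of an outcome scale is usually among the best predictors of its later value. Here it is collected at no extra cost and then not used as a predictor. The Discussion promises insight into which children are at risk of long-term participation problems. Part of that question is whether a symptom scale or an injury feature says anything more once it is known how the child is participating at 2 weeks. The planned models cannot answer this, because a T0 scale that simply tracks early participation looks the same in them as one that carries separate information. The linear model also gives up whatever outcome variance the T0 score would explain.

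**Working it through.** **The plan's own figures (Sample size).** 500 × (1 − 0.10) = 450 analysed; 0.20 × 450 = 90 with long-term problems; 90 / 10 = 9 determinants. All three reproduce, and this point disputes none of them.

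**Is the gap filled elsewhere?**
- CAPE is the only participation measure among the predictors. The article's section on CAPE reports no significant correlation with the CASP-DLV parent version, so it cannot stand in.
- The repeated-measures analysis of variance in the cohort section describes change over time but contains no predictors.
- PedsQL-QoL carries part of the information: under Primary outcome measure, the correlation of CASP-DLV with PedsQL is given as 0.45.
- T0 CASP-DLV is a post-injury score (Outcome measurements). HBI, fatigue, quality of life, post-traumatic stress and CAPE at T0 are post-injury too, and they are admitted. Being measured after the injury therefore does not explain the omission.

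**Residual SD of the linear model.** Let r be the T0–T2 correlation of the CASP-DLV parent report. The documents do not give it; 0.3 to 0.7 is an assumption. Against a model with no other covariates, adding T0 CASP-DLV multiplies the residual SD by √(1 − r²). For a predictor unrelated to T0 CASP-DLV, the equivalent sample size is 450 / (1 − r²).

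| r | variance explained, r² | residual SD factor | fall | equivalent N |
|---|---|---|---|---|
| 0.3 | 0.09 | 0.954 | about 5% | 495 |
| 0.5 | 0.25 | 0.866 | about 13% | 600 |
| 0.7 | 0.49 | 0.714 | about 29% | 882 |

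These falls are practical ceilings, because the other T0 scales will already explain some of the same variance.

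**Precision of a single coefficient.** Take a predictor correlated ρ with T0 CASP-DLV and related to the 6-month score only through it. The ratio of its standard error with T0 CASP-DLV to that without is √[(1 − r²) / ((1 − ρ²)(1 − ρ²r²))]. With ρ = 0.45, borrowed from the PedsQL correlation as an illustration:
- r = 0.3: √[0.91 / (0.7975 × 0.9818)] = 1.08
- r = 0.5: √[0.75 / (0.7975 × 0.9494)] = 0.995
- r = 0.7: √[0.51 / (0.7975 × 0.9008)] = 0.84

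So precision is slightly worse, unchanged or better, depending on r.

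**How differently the two models answer.** For the same predictor (ρ = 0.45), 2,000 simulated data sets of 450 children gave p < 0.05 in 81%, 99.9% and 100% of runs without T0 CASP-DLV (r = 0.3, 0.5, 0.7), and in about 5% with it. The predictor was built to act only through the early level. The contrast shows that the models address different questions; it is not an error rate for the planned one.

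**The case against.** The strongest defence is that the plan asks about the level at 6 months. The Background hypothesises only that injury-related and non-injury-related factors predict outcome. Nothing in the article asks for predictors of change or for prediction conditional on early participation. For Glasgow Coma Scale score, amnesia, loss of consciousness, pre-injury behaviour and pre-injury family functioning, the 2-week score lies downstream, so adjusting for it can remove part of the effect of interest. The Background also says that children with MTBI typically get no follow-up care, so a 2-week CASP-DLV would not normally be to hand in practice. All of this stands, and it is why the model without T0 CASP-DLV must stay.

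A reader might go further and infer that predictors found by the planned models would be false positives, that precision is lost throughout, or that T0 CASP-DLV has to be forced into a single main model. The documents support none of these. A scale that tracks low early participation, where that persists, truly is associated with the 6-month level. The standard-error ratios above show no assured gain. A forced single model would obscure the factors named in the Background.

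It can also be said that a condensed article leaves covariate detail to the analysis plan. That mitigates little here, because the article names the candidates instrument by instrument and fixes the selection rule.

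**Conclusion.** The point holds as a cheap improvement to the cohort aim. The candidate list omits an available and likely strong predictor, the T0 value of the outcome scale itself, while admitting other post-injury T0 scales. The planned models remain valid for association with the 6-month level, but they cannot show what adds to participation at 2 weeks. The possible reduction in residual SD, at most about 5% to 29%, rests on the assumed T0–T2 correlation of 0.3 to 0.7 and applies to the linear model only; no gain was calculated for the logistic model. No stated figure changes, and the RCT sample size is not touched.

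**What to change.** Add the T0 CASP-DLV parent report to the candidate predictors in the cohort section. Report the multivariable linear and logistic models in two forms:
- without T0 CASP-DLV, for the total association of injury and pre-injury factors with the 6-month outcome;
- with T0 CASP-DLV, for prediction beyond early participation.

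Count it as one of the nine determinants, and state which question each model answers.

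The cost is a line or two of text and a second set of results; no new data are needed. There are two downsides. It takes one determinant place, leaving eight for the others in the model that contains it. And that model may absorb effects of injury and pre-injury factors that run through early participation, so it should stand beside the model without it and not replace it.

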### Sample size

Sample size calculations for the cohort study are based on the available literature about MTBI prevalence and the expected number of participants who may visit the participating hospitals. Based on an inclusion period of 2 years, the aim is to recruit a sample of 500 children and adolescents who have experienced an MTBI. Assuming a 10 % dropout rate [64], our final sample should include 450 participants. Previous research shows that approximately 20 % of the population will experience long-term problems [13–16, 20–24, 30, 36] after an MTBI. Therefore, approximately 90 of our participants will experience long-term problems. When conducting the regression analysis to identify the predictors of the presence of long-term problems, we should include nine determinants, based on the assumption that approximately ten participants per determinant are needed for a reliable analysis [65].

Sample size calculations for the RCT are based on the results of studies on paediatric traumatic brain injury patients’ participation that relied on the parent-reports of the CASP-DLV. For the CASP-DLV, a standardized difference of 0.5 was expected [48]. With an α of 0.05 and a power of 0.8, a minimum of 63 children per group (control group and intervention group) is required for sufficient statistical power. Assuming a dropout rate of 10 %, the aim is to recruit at least 140 children and adolescents for the RCT.

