To the authors’ knowledge, this is the first study to examine the effect of an early individualized psychoeducational intervention designed to prevent activity and participation problems in a relatively large group of children and adolescents following an MTBI. All of the participants in the nested RCT design receive usual care, and the intervention group receives an additional intervention. The intervention has a specific theoretical basis, and its design is based on evidence from the literature. Finally, and perhaps most importantly, the intervention is created to suit clinical practice and can be applied easily and directly in daily practice after its effectiveness has been proven. The results of this study will provide insight into which children with MTBI are at risk for long-term participation problems and may benefit from a psychoeducational intervention.

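### Cohort predictors are chosen by p value and their effects read from the same data, so weak and moderate predictors that reach significance will look stronger than they are

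*Protocol article*

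**What the plan says.** The Cohort study subsection of the statistical analyses sets out the predictor analysis: "Linear regression analysis will be used to identify the outcome predictors of activities and participation at 6 months post-injury". Each baseline variable is first tested alone. Variables with p<0.2 "in the univariate linear regression analysis will be included in the multivariate linear regression analysis", and the significance level in that model is p<0.05. Logistic regressions are added for clinical relevance, without a stated selection rule.

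The Sample size section says of the predictor regression that "we should include nine determinants, based on the assumption that approximately ten participants per determinant are needed for a reliable analysis". The candidate list is longer. Table 1 has seven injury-related and nine non-injury-related variables, and the Cohort study subsection adds six baseline instruments (fatigue, quality of life, sensory processing, post-concussive symptoms, post-traumatic stress and after-school participation).

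On the use of the results, the Discussion says: "The results of this study will provide insight into which children with MTBI are at risk for long-term participation problems".

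**The concern.** A factor with a small true effect crosses p<0.05 mainly in samples where its estimate happens to be large. If its coefficient is then read from the same model and the same children, it is biased away from zero on average, and its ordinary confidence interval ignores the selection. The fit of a model built this way is also better in the cohort that built it than in new children. Identifying predictors is part of the study's first aim. Risk factors could therefore appear stronger and more usable than they are. The randomised comparison is not affected.

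**Working it through.** **1. The plan's own figure.** Inputs from the Sample size section: 500 recruited, 10% dropout, 20% with long-term problems, ten per determinant.
- 500 × 0.90 = 450 ("our final sample should include 450 participants")
- 450 × 0.20 = 90 ("approximately 90 of our participants will experience long-term problems")
- 90 / 10 = 9 determinants. This reproduces.

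**2. What is screened.** 7 + 9 + 6 = 22 variables, more once multi-category factors and subscales are counted. Events per candidate: 90 / 22 = 4.1, not 10. If the intervention group is excluded, as the article foresees when the intervention proves effective, 63 to 70 children leave. Then 380 to 387 remain, with 76 to 77 events, which supports seven determinants by the same rule.

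**3. Why selection inflates.** Take independent standardised candidates and residual SD 1. The standard error is about 1/√450 = 0.047, so p<0.05 needs an estimate above about 1.96 × 0.0471 = 0.092. Ignoring the wrong-sign tail, the mean reported estimate is β + SE × φ(a)/(1 − Φ(a)), with a = 1.96 − β/SE.
- β = 0.05: a = 0.90, mean 0.118, ratio 2.36
- β = 0.10: a = −0.16, mean 0.133, ratio 1.33
- β = 0.20: a = −2.28, mean 0.201, ratio 1.01

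**4. Simulation of the full two-step rule.** N=450; true coefficients 0.20, 0.10, 0.10, 0.05, 0.05 and the rest zero; normal covariates; 9 or 22 candidates; correlation 0 or 0.3. Ratio of mean estimate to true value when significant, over these settings:

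| True effect | Ratio |
|---|---|
| 0.20 SD | 0.99 to 1.02 |
| 0.10 SD | 1.31 to 1.52 |
| 0.05 SD | 2.3 to 2.7 |

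For reported 0.05 SD effects, nominal 95% intervals covered the truth in 81 to 87% of cases.

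**5. Fit.** R-squared of the model holding every variable that passed the screen, with independent candidates: 0.074 apparent against 0.040 in new data with nine, and 0.089 against 0.023 with 22.

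**6. Second set of assumptions.** Four equal true effects, correlation 0.2, 22 candidates, linear model:

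| True effect | Ratio when significant | R-squared, apparent vs new data |
|---|---|---|
| 0.08 | 1.65 | 0.063 vs 0.015 |
| 0.15 | 1.10 | 0.157 vs 0.087 |
| 0.25 | 1.00 | 0.320 vs 0.255 |

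If the logistic model (20% events) followed the same rule, log odds ratios per SD of 0.2, 0.35 and 0.5 would be inflated 1.71, 1.21 and 1.11 times. AUC would be 0.670 vs 0.611, 0.749 vs 0.703 and 0.814 vs 0.765.

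**7. Do the remedies work?**
- *Bootstrap of the whole procedure.* Corrected R-squared = apparent R-squared minus the mean of (R-squared in the bootstrap sample minus R-squared of that bootstrap model in the original sample). Corrected against true values in the four settings of step 4: 0.039 vs 0.040, 0.090 vs 0.089, 0.015 vs 0.023 and 0.078 vs 0.064.
- *Nine prespecified predictors, all kept* (assumptions of step 6). Mean coefficient over true value is 0.99 to 1.01 in the linear model and 0.99 to 1.05 in the logistic, so the selection bias goes. Fit remains optimistic (linear, weak effects: 0.059 vs 0.017) and still needs correction.
- *One uniform shrinkage factor.* The 0.20 SD effect falls to 0.74 to 0.93 of its true value, while 0.05 SD effects stay 1.7 to 2.4 times too large.

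**The case against.** The strongest reply is that the absence of shrinkage or internal validation is only the article's silence, and such steps may stand in a fuller protocol or analysis plan. That is right as far as it goes. A reader might infer that the sponsor plans no correction; the article neither states nor excludes one. What the article does state is the selection rule, and following it produces the bias.

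Second, a reader might infer that the study promises a risk score for new children. It does not. It announces no R-squared, AUC or classification, speaks of identifying predictors and of insight, and does not say that the model is refitted with the significant factors only. The point on fit therefore applies only if such figures are reported; the point on coefficients does not need them.

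Third, the logistic figures assume a selection rule that the article attaches only to the linear model. The events count in step 2 likewise concerns the presence of long-term problems. For the linear model there are 450 / 22 = about 20 children per candidate, so that ratio does not by itself condemn the linear analysis.

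Fourth, the largest ratios belong to very small effects. In one rerun a 0.05 SD effect reached significance in only about 8 to 21% of samples. With nine candidates and moderate or strong effects (0.15 and 0.25) in the linear model, coefficients were overstated by 0 to 9% and R-squared by about 0.02 to 0.03. This stands and limits the size of the point.

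**Conclusion.** The concern holds in a limited form. The stated two-step rule, applied to at least 22 listed variables at N=450, overstates weak and moderate predictors that reach significance: about 1.3 to 1.5 times at 0.10 SD and 2.3 to 2.7 times at 0.05 SD. It does not support the claim that all predictors are overstated, since a 0.20 SD effect is essentially unbiased. Any fit reported from the same data would be optimistic, and more so with 22 candidates than with nine. The direction is secure; the sizes rest on assumed effect sizes, correlations and normal covariates, none of which the article gives. This is a worthwhile and cheap improvement to the predictor analysis, not a flaw that invalidates the cohort.

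**What to change.** In the Cohort study subsection of the statistical analyses:
- Repeat the whole procedure (p<0.2 screen and multivariable step) in bootstrap samples and report how often each factor is selected.
- Wherever model performance is reported, give the optimism-corrected R-squared or AUC.
- Report all coefficients of the full multivariable model beside the significant ones. Preferably fit it to the nine prespecified determinants that the sample size section says the cohort supports, without the p-value screen (seven by the same rule if the intervention group is excluded).
- State whether the logistic models follow the same selection rule.
- Do not multiply individual coefficients by one uniform shrinkage factor as a cure for selection bias; it over-shrinks strong predictors and leaves weak ones inflated.

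Base the Discussion's statement on which children are at risk on these figures. The cost is a few hours of analysis and a few sentences of text, with no new data. The downside is that reported performance will look slightly less favourable.

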### Outcome measurements

Several injury-related and non-injury-related variables are identified. These variables are presented in Table 1 and Fig. 3.

**Table 1 Tab1:** Injury/non-injury-related variables

Injury-related variables
Glasgow Coma Scale score (first recorded in the ambulance or ED)
Post-traumatic amnesia duration in minutes
Loss of consciousness reported in ED
Change in mental functioning: post-acute confusion or disorientation
Other transient neurological abnormalities
CT/MRI/EEG abnormalities
Cause of MTBI
Non-injury-related variables
Location (hospital where MTBI was diagnosed)
Admission to hospital
Age of patient at injury
Gender
Education level of patient
Pre-injury behavioural and emotional problems of the patient (measured using the CBCL)
Parental socioeconomic status
Pre-injury family function (measured using the FAD-GF)
Family situation (number of family members residing with the patient)

*ED* emergency department, *CBCL* Child Behaviour Checklist, *FAD-GF* Family Assessment Device–General Functioning Scale

The instruments used to measure activity and participation after an MTBI and possible outcome predictors are presented in Fig. 3, as well as in Table 2 for patients and in Table 3 for caregivers, and are described in more detail hereafter. All instruments described below are completed based on post-injury functioning, unless stated otherwise. Given the fact that a subset of the cohort sample will receive the intervention, this might influence the outcome data in the cohort study. Therefore, if the intervention is found to be effective, the outcome data of the intervention group will be excluded from all cohort analyses (see Statistical analyses subsection below).

**Table 2 Tab2:** Outcome domains, measurement instruments and measurement moments for the patients with mild traumatic brain injury

Domain	Measurement instrument	Abbreviation	Age (years)	T0	T1	T2
Activities and participation	Children’s Assessment of Participation and Enjoyment	CAPE	6–18	X	X	X
	Child and Adolescent Scale of Participation–Dutch language version	CASP-DLV	10–18	X	X	X
Quality of life	PedsQL–Quality of Life Scale	PedsQL-QoL	6–18	X		X
Fatigue	PedsQL–Multidimensional Fatigue Scale	PedsQL-Fatigue	6–18	X		X
Health and behaviour	Health Behaviour Inventory	HBI	8–18	X		X
Post-traumatic stress	Schokverwerkingslijst (Impact of Event Scale–Dutch language version)	SVL (IES)	8–18	X		X

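### Whether the intervention arm stays in the cohort depends on the RCT's significance test, and the cohort figures of 450, 90 and nine make no allowance for the exclusion that the RCT's own planning makes likely

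*Protocol article*

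**What the plan says.** The rule appears twice in the protocol article. Under Statistical analyses, Cohort study: "If the intervention is found to be effective (see statistical analyses of RCT study below), the data of the intervention group will be excluded"; the sentence goes on to cover every cohort analysis. Under Outcome measurements: "if the intervention is found to be effective, the outcome data of the intervention group will be excluded from all cohort analyses". The reason is given just before: "Given the fact that a subset of the cohort sample will receive the intervention, this might influence the outcome data in the cohort study". The RCT subsection sets the significance level at p < 0.05.

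The cohort figures are in the Sample size section. On recruitment, "the aim is to recruit a sample of 500 children and adolescents who have experienced an MTBI". Then "Assuming a 10 % dropout rate [64], our final sample should include 450 participants". Then "Previous research shows that approximately 20 % of the population will experience long-term problems", and so "approximately 90 of our participants will experience long-term problems". At about ten such participants per determinant, the section arrives at nine determinants.

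The same section sizes the RCT for a standardised difference of 0.5 with 80% power: 63 per group, 140 recruited after allowing for 10% dropout. The Abstract and the Study design section make clear that these 140 are part of the 500.

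**The concern.** The reason for the rule and its trigger do not match. The worry is that treatment changes the outcomes of some cohort members. That depends on whether the intervention works, whereas the trigger is whether one trial of limited size shows that it works. A missed true effect leaves treated children in the cohort, which is what the rule was written to avoid. A false positive removes about 70 children for no reason.

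Two things are at stake. First, the population behind the first aim (course, frequency and predictors of participation problems) is not fixed in advance: it is either usual care alone or usual care mixed with psychoeducation, depending on a test result. Second, the Sample size section plans an RCT that is expected to succeed, yet counts the cohort as if the exclusion that follows from success could not occur.

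**Working it through.** **The plan's own figures.** Cohort: 500 × 0.90 = 450; 450 × 0.20 = 90; 90 / 10 = 9. RCT, two-sided α 0.05 (sidedness is not stated, but two-sided reproduces the figure): 2 × (1.960 + 0.842)² / 0.5² = 62.8, so 63 per group; 126 / 0.90 = 140, or 70 per arm with equal allocation. All reproduce, and the cohort figures use all 500 recruits.

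**How often the rule removes the arm.** The RCT comparison is approximated by a two-sample test with 63 per arm, where the standard error is √(2/63) = 0.178 SD.
- True effect 0.5 SD: 0.5 / 0.178 = 2.81; Φ(2.81 − 1.96) ≈ 0.80. Excluded about 80% of the time, kept about 20%.
- True effect 0.3 SD: excluded about 39%, kept about 61%.
- True effect 0.25 SD: 0.25 / 0.178 = 1.40; Φ(1.40 − 1.96) ≈ 0.29. Excluded about 29%, kept about 71%.
- No effect: excluded 5% of the time on one test.

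**If the arm is excluded.** (500 − 70) × 0.90 = 387 analysed; 387 × 0.20 = 77.4 with long-term problems; 77.4 / 10 = 7.7, so 7 determinants. Nine determinants would have 77.4 / 9 = 8.6 events each. Sample and events both fall by 14%. The linear regression would still have 387 / 9 = 43 children per determinant.

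**If the arm is kept although the intervention works.** The treated share is 63 / 450 = 14%. The cohort mean shifts by d × 0.14:
- d = 0.25: 0.035 SD
- d = 0.5: 0.07 SD

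Events also fall below 90. The protocol gives no risk for treated children, so these are assumptions:
- Treated risk 15%: 387 × 0.20 + 63 × 0.15 = 86.9
- Treated risk 10%: 77.4 + 6.3 = 83.7, a cohort prevalence of 83.7 / 450 = 18.6%
- Treated risk 5%: 77.4 + 3.2 = 80.6

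At ten events per determinant, each of these supports 8 determinants, not nine. So whenever the intervention lowers the risk to this extent, 90 and nine are not reached, whether the arm is kept or removed.

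**The case against.** The strongest reply is that the harm is small. The rule is written down in advance, in two consistent places, with its reason. The shift if the arm is kept (0.035 to 0.07 SD) is below the 95% half-width for a mean of 450 children, 1.96 / √450 = 0.09 SD. The fall in prevalence from 20% to 18.6% is well inside a half-width of 3.7 percentage points. The rule also limits itself in part: the larger the effect, the more likely the arm is removed. All of this stands, and it lowers the severity.

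A reader might be tempted by stronger readings, which the protocol does not support:
- *That the cohort population is chosen post hoc.* The rule is prespecified and its trigger is the RCT comparison, not the cohort's own predictor results. The fault is that the rule hangs on a noisy test.
- *That treated children stay in only when a real effect is missed.* They also stay in, 95% of the time on one test, when there is no effect and keeping them does no harm.
- *That all predictor analyses are short of data.* The ten-per-determinant count concerns the presence of long-term problems. The linear regression on the CASP-DLV score, which the article names first, is not limited by events. For the other model, 8.6 against approximately ten is a moderate shortfall.
- *That the trigger is undefined because effectiveness is assessed at both 3 and 6 months.* Which contrast counts is a detail that an analysis plan, not shown here, may settle.

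It is also fair to say that the 20% rate is itself uncertain: the Background cites 6% to 43% with continuing symptoms. That does not justify leaving out a loss of 70 children that the plan itself prescribes.

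**Conclusion.** The point holds in moderate form. A test with about 80% power at 0.5 SD and about 29% at 0.25 SD decides whether the cohort is usual care alone or about 14% treated, although a non-significant result does not answer the worry about treatment influence. The resulting bias is modest. The figures of 450, 90 and nine are inconsistent with the exclusion that the RCT's planning assumption makes likely; with the arm removed they become about 387, 77 and 7, the last for the presence-of-problems model only.

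This rests on equal allocation of exactly 140 children (the article says at least 140), 10% dropout in both parts, a 20% problem rate among children not assigned to the intervention, and a two-sample approximation to the planned multilevel model. The RCT's randomisation, test and conclusion are untouched. This is a should-fix, not a must-fix.

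**What to change.** Make the change before the RCT result is known.

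1. **Outcome measurements and Statistical analyses, Cohort study.** Replace the conditional exclusion with a rule that does not depend on the RCT. The primary set for the course, prevalence and predictor analyses is all children not assigned to the intervention: RCT controls and non-RCT children.
2. **Sensitivity analysis.** Repeat the analyses in all children, with hospital and an indicator for assignment to the intervention (1 = intervention arm, 0 = RCT control or non-RCT child). Randomised group itself cannot serve as the covariate, because it is undefined for the 500 − 140 = 360 children who are never randomised.
3. **Sample size.** Restate the cohort figures as about 387 analysed, about 77 with long-term problems, and at most 7 determinants for the presence-of-problems model. No additional recruitment is asked for; holding 450, 90 and nine after exclusion would need 500 + 70 = 570.

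The cost is wording in three places, about 14% fewer children in the primary cohort analyses, and somewhat less weight for the two RCT hospitals. The plan already accepts the same loss whenever its intervention is found effective.
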